#### 2.3.2. Secondary Outcomes

In the surgical group, we will assess associations between glycaemic patterns and the risk of adverse pregnancy outcomes, including SGA and birth defects. Linear mixed models will be used analogously to the primary analysis, with adverse pregnancy outcomes as explanatory variables in the models. Additional analyses will assess the association of hypoglycaemia as a binary variable with birth weight or adverse pregnancy outcomes. generalised linear mixed models for binary outcomes will be used for data analysis.

#### 2.3.3. Exploratory Outcomes

An overview of clinical definitions and diagnostic criteria considered in this study is given in a supplemental table, Table S1. The self-designed questionnaire on the user-friendliness of the masked CGM for both groups is given in Tables S2 and S3. These outcomes will be analysed for both the surgical and the control group.

-Maternal glycaemic outcomes: percentage of time < 54 mg/dL (ADA recommendations of the definition of hypoglycaemia) [24]; glycaemic variability metrics: standard deviation (SD), Coefficient of Variation (CV) and Mean Amplitude of Glucose Excursions (MAGE); percentage of time > 120 mg/dL; percentage of time > 140 mg/dL; percentage of time > 180 mg/dL; percentage of time < 70 mg/dL; percentage of time < 63 mg/dL; percentage of time < 50 mg/dL; low blood glucose index (LBGI)-Maternal pregnancy outcomes: duration of pregnancy; time from surgery to conception; prevalence of micro- and macronutrient deficiencies; body composition in early pregnancy as assessed by bio-impedance measurement, prevalence of GDM; gestational weight gain (GWG); prevalence of caesarean section; prevalence of pre-eclampsia and eclampsia, prevalence of gestational hypertension; surgery-related complications during pregnancy; type of labour; type of delivery; complications during delivery-Foetal growth and body composition outcomes: prevalence of SGA; large for gestational age (LGA); prevalence of intra-uterine growth retardation (IUGR); FASTT; pregnancy loss-Neonatal outcomes: body composition of the newborn assessed by skin fold thickness measurements, according to [25]; prevalence of preterm delivery; prevalence of neonatal hypoglycaemia; prevalence of neonatal intensive care unit (NICU) admission; foetal malformation; complications during delivery; sex of the infant; birth weight, length, and percentile; neonatal death-Identification of new biomarkers: metabolomics on maternal plasma collected at 30–34 weeks: lipid omics platform and metabolism and energy platform. We will prioritise analyses for the surgical group.-Patient-reported outcomes: certain potential confounders, such as smoking status, will be derived from survey data. Additionally, other patient-reported outcomes collected through the surveys will be analysed as independent outcomes in the exploratory comparisons between subgroups. The following questionnaires will be completed at the different study visits:A self-designed questionnaire on general habits and socio-economic background previously used in the Belgian Diabetes in Pregnancy study (BEDIP) to extensively collect information on socio-economic status and habits [22].A self-designed questionnaire on the user-friendliness of the masked CGM, based on the CGM Satisfaction Scale (CGM-SAT) [26], the Glucose Monitoring Experiences Questionnaire (GME-Q) [27], and the Glucose Monitoring Satisfaction Survey (GMSS) [28].Frequency Food questionnaire (FFQ), including questions on frequency and portion size of consumed foods and beverages validated for the Belgian population [29].International Physical Activity Questionnaire (IPAQ, full version) validated for use in the Belgian population and as used in the BEDIP study [22]. This questionnaire assesses various domains of physical activity, including job-related tasks, caregiving, and time spent sitting.The 36-Item Short Form Health Survey (SF-36) includes a set of generic, coherent, and easily administered quality of life measures and is validated for use in the maternity context [30].The 20-item Centre for Epidemiologic Studies-Depression (CES-D) questionnaire, which is validated in pregnancy to asses symptoms of clinical depression over the past seven days [31].The State-Trait Anxiety Inventory (STAI) questionnaire, a validated six-item short-form on anxiety, which is validated for the Dutch speaking population [32].

### 2.4. Recruitment and Eligibility

Participants will be recruited from eight gynaecology and obstetrics departments in Belgium. The planned recruitment period is two and a half years. Written informed consent will be obtained at each site before any study-related activities are performed. Participants will be eligible if they fulfil the following criteria:

#### 2.4.1. Inclusion Criteria

-age 18–45 years-singleton pregnancy with ultrasound-confirmed gestational age up to eleven weeks and six days-for the group with MBS: history of SG or RYGB-participants need to speak and understand Flemish, French, or English and have e-mail access

#### 2.4.2. Exclusion Criteria

-multiple pregnancy-pregnancy beyond 12 weeks at time of inclusion-other types of MBS than SG or RYGB-known pregestational diabetes mellitus-medications known to interfere with glucose metabolism, at time of inclusion-a physical or psychological disease likely to interfere with the conduct of the study

### 2.5. Groups

#### 2.5.1. After Metabolic Bariatric Surgery

Pregnant women after SG or RYGB.

#### 2.5.2. Control

Pregnant women with no history of MBS who meet the inclusion criteria can participate if matched with a participant from the surgical group. Controls will be manually matched 1:1 based on age and pre-pregnancy BMI in early pregnancy (before twelve weeks).

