## 2. Methods

### 2.1. Study Design and Setting

The GLORIA study is a prospective cohort study involving eight Belgian sites, investigating pregnancy outcomes following sleeve gastrectomy (SG) or RYGB. In a second stage, outcomes will be compared to a matched control group using an exploratory approach. SG has increasingly become the first-choice type of MBS for women of reproductive age. We estimate that between 30 and 50% of participants will have SG in the study. For each participant in the surgical cohort, an age- (≤2 years difference, and age > 40 will be rounded to 40 years) and BMI-matched (≤2 BMI points difference, matched to pre-pregnancy BMI) pregnant woman without history of MBS will be recruited. Seven Belgian hospitals were originally included to take part in the study: three university hospitals (UZ Leuven, UZ Antwerpen, and UZ Gent) and four large non-university hospitals (ZAS Palfijn, AZORG Aalst, Imelda Bonheiden, and AZ St-Jan Brugge). In 2023, one additional centre was added. All eight centres have previously participated in multicentre studies initiated by our research group [22,23]. Participating centres were selected for their expertise in endocrinology research, as well as obstetrical management of pregnant women with a history of MBS.

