#### 2.8.1. Screening Visit

The study will be introduced at first prenatal visit by a physician or midwife. Interested women will receive a summary information sheet and the informed consent form. Women will have at least 24 h to consider their decision, after which the local research team will follow up on their choice. Informed consent can only be signed if all inclusion and exclusion criteria have been met. Pregnant women can only participate in the control group if a one-on-one match is identified with a participant in the surgical group. The coordinating investigator will maintain a password-protected log containing BMI and age data for all study participants to ensure accurate matching.

#### 2.8.2. Visit 1 to 4

Women will be recruited at first prenatal visit (before 12 weeks). To evaluate glucose homeostasis, a masked CGM will be used for 10 days at the following time points: between 6 and 12 weeks of pregnancy, at 18–22 weeks of pregnancy, at 24–28 weeks of pregnancy (when screening for GDM, and at 30–34 weeks of pregnancy. At each visit with CGM, clinical examination will be performed, questionnaires will be completed, and micronutrients will be measured (as described below). As standard of care in the surgical group, follow-up by a dietician during pregnancy will be provided according to need or at the indication of the treating physician. A purpose designed multivitamin preparation (BariNutrics^®^ Prenatal) will be started at periconception. In each trimester, micronutrients will be checked by blood analyses of vitamin A, vitamin D, B12, folate, prothrombin time iron, transferrin saturation, and ferritin, for the surgical group. Deficiencies detected at any time point will be addressed by the prescription of targeted extra supplementation by the treating physician.

A standardised protocol will be used to screen for diabetes in early pregnancy and GDM later in pregnancy for both groups.

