#### 2.8.8. Cord Blood

Venous cord blood (3 samples) will be collected at delivery in each participating centre by a midwife or obstetrician. Cord-blood will be obtained by free drainage (free flow) or drawn by needle aspiration (puncture) from a clamped segment of an umbilical vein. In each centre, cord blood will be stored locally at −20 °C and transported to UZ Leuven for storage at −80 °C at the biobank of UZ Leuven until analyses. Samples will be stored for max. 10 years.

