#### 2.8.10. Ultrasound Measurements

To evaluate foetal anatomy, growth, body composition, and placental function, detailed ultrasound examination according to current ISUOG guidelines will be performed by trained sonographers at approximately 12, 20, and 32 weeks of gestation (Table 1). Training of the sites will be provided by an obstetrician from UZ Leuven, who has extensive experience in ultrasound measurements in pregnant women with obesity and after bariatric surgery.

Participating centres will detach dedicated sonographers trained in routine sonographic measurements. For specific study measurements including FASTT, detailed standard operating procedures (SOPs) will be available to the research teams. Training sessions will be organised. Digital images of foetal measurements will be stored. In the data management phase, we will evaluate measurements by individual sonographer and study centre to further exclude abnormal variability (both internal and external).

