##### Exploratory Comparative Analyses

The control group will be manually matched in a 1:1 ratio based on age and pre-pregnancy BMI before participation. A comparison of both groups on participant characteristics such as parity, insufficient GWG, hypertension, micronutrient deficiencies, and smoking status will be performed using Fisher exact tests. The comparison between the MBS and control group on birth weight and glycaemic measures will be performed using linear mixed models with a random intercept to account for clustering by matching. Confounders will be included as covariates in the model in case they were shown to differ between groups. Group comparisons on binary variables such as adverse pregnancy outcomes will be performed using a similar approach, applying generalised linear mixed models for binary responses.

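### Controls are matched on age and BMI but not on centre, and the group-comparison model names no centre term, so unequal centre mixes can bias the exploratory surgery-versus-control comparison

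*Protocol article*

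**What the plan says.** Section 2.1 of the Protocol article sets the matching tolerances: two years of age, with ages above 40 counted as 40, and for BMI: "BMI-matched (≤2 BMI points difference, matched to pre-pregnancy BMI) pregnant woman without history of MBS will be recruited". Section 2.5.2 repeats the two factors: "Controls will be manually matched 1:1 based on age and pre-pregnancy BMI in early pregnancy (before twelve weeks"). Section 2.8.1 says how matches are found: "The coordinating investigator will maintain a password-protected log containing BMI and age data for all study participants to ensure accurate matching". No section lists centre as a matching factor or as a field of that log, although section 2.4 states: "Participants will be recruited from eight gynaecology and obstetrics departments in Belgium".

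Under Exploratory Comparative Analyses in 2.9.2, birth weight and glycaemic measures are compared between groups with "linear mixed models with a random intercept to account for clustering by matching". Binary outcomes get a similar approach. Covariates enter only if they were shown to differ between groups. The characteristics given as examples are parity, insufficient gestational weight gain, hypertension, micronutrient deficiencies and smoking.

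Centre does appear in 2.8.10, for ultrasound, at the data-management stage: "we will evaluate measurements by individual sonographer and study centre to further exclude abnormal variability (both internal and external").

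**The concern.** A matched-pair intercept removes a centre difference only when both women of a pair belong to the same centre. The text does not require that, and no centre term stands behind the intercept. If one centre supplies a larger share of controls than of surgical women, whatever is particular to that centre is carried into the group difference.

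Some outcomes of the control phase are sensitive to this. Each centre's own sonographers measure FASTT. Study staff take skinfolds by caliper, and the effect of surgery on newborn body composition is a listed objective (2.3). Caesarean section and NICU admission (2.3.3) can follow local practice, and the sites include both university and non-university hospitals (2.1). Masked CGM is less exposed: it uses one device (2.8.9), and the metrics are derived from data exported at the coordinating site (2.9.5).

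At stake is whether a difference in these outcomes can be attributed to surgery rather than to where the women were seen.

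**Working it through.** **The plan's own figure.** The only sample size in the article is 95 surgical women for the primary association (2.9.1). It reproduces. For a correlation of 0.3, two-sided alpha 0.025 and power 0.80, ((2.2414 + 0.8416)/atanh(0.3))² + 3 = 102.2. Adding 4 for the covariates gives 106.2. The design effect is 1 + (4 − 1) × 0.5 = 2.5. Then 106.2 × 2.5 / 4 / 0.7 = 94.8, so 95. That figure concerns the surgical group alone and does not depend on matching. The article gives no power or sample size for the group comparison.

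**Inputs for the check.**
- From the article: 8 centres; 1:1 matching, so 95 per group if every surgical woman is matched; two-sided 5% tests.
- Assumed: centres account for 2%, 5% or 10% of outcome variance; surgical women are spread evenly over the centres; there is no true group difference.

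**Formula.** Let p_k and q_k be the shares of surgical and control women at centre k, and c_k the centre's deviation in units of outcome SD. Without a centre term,

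bias = Σ (p_k − q_k) c_k, with SD = √(v × Σ(p_k − q_k)²), where v is the centre share of variance.

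The standard error of the group difference is √(2/95) = 0.145 SD. Averaged over centre deviations, the error rate is approximately 2Φ(−1.96 / √(1 + (bias SD/0.145)²)).

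1. Equal mixes: Σ(p_k − q_k)² = 0, so the bias is zero.
2. Control mix drawn at random (uniform Dirichlet over 8 centres): the expected sum is 8 × (1/8 × 7/8)/9 = 0.0972.
3. All controls from one centre: (7/8)² + 7 × (1/8)² = 0.875.

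| Control mix | Centre share of variance | Bias SD | Error rate, formula | Error rate, simulation |
|---|---|---|---|---|
| Equal | 2 / 5 / 10% | 0 | 5% | 5.8 / 4.2 / 5.0% |
| Random | 2% | 0.044 | 6.1% | 6.4% |
| Random | 5% | 0.070 | 7.7% | 7.7% |
| Random | 10% | 0.099 | 10.5% | 10.5% |
| One centre | 2% | 0.132 | 14.8% | 15.7% |
| One centre | 5% | 0.209 | 26.4% | 26.4% |
| One centre | 10% | 0.296 | 38.8% | 40.1% |

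The simulation used 3,000 runs per cell and a two-sample test. For pairs formed across centres without regard to centre, this stands in for the matched model; correlation within pairs from age and BMI was not simulated. A control mix halfway between equal and random gave 5.3–6.3%.

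**With the remedy.** Centre as a fixed effect gave 4.4–5.9% under the equal, halfway and random mixes. Same-centre pairs without a centre term gave 4.2–5.1%.

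**Why the model term alone may not be enough.** If all controls came from one centre, the within-centre contrast would rest on the roughly 95/8 ≈ 12 surgical women there. Its standard error would be √(8/95 + 1/95) = 0.308 SD, against 0.145 SD, or about 2.1 times as large. Adjustment cannot create overlap that recruitment did not provide.

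**The case against.** The best defence has five parts.

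*The comparison is exploratory.* This stands. The article says so repeatedly, and the primary and secondary analyses in 2.9.2 use the surgical group only. It limits the weight of the point. It does not make a systematic difference harmless, since section 3 offers these data for later meta-analyses.

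*The stated model covers birth weight, glycaemic measures and binary outcomes, and no model is given for FASTT or skinfolds.* This also stands: how those two will be modelled may be written elsewhere. The matching rule, however, governs every control-phase outcome.

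*A centre term is a usual analysis-plan detail, and the list of characteristics is open-ended.* This holds in part. Centre is not ruled out. But the stated rule admits covariates only after a test shows a difference, and such a test can miss a moderate imbalance over eight centres. Same-centre matching is a design decision taken before a control enters, and a later analysis plan cannot supply it.

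*Measurement is standardised.* There are trained sonographers, written FASTT procedures, stored images, a named skinfold caliper and quality visits. These should make centre differences smaller. The review by sonographer and centre covers ultrasound only and adjusts nothing.

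*Tight tolerances and the 12-week limit make same-centre matching hard.* This is fair, and it is why a fallback is needed.

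A reader might infer more than the text supports:
- **That pairs do cross centres.** The article permits this but does not say that it happens.
- **That cord-blood results are at risk.** No cord-blood outcome is listed for the control phase, and 2.8.8 sets one storage rule for all sites: "In each centre, cord blood will be stored locally at −20 °C and transported to UZ Leuven for storage at −80 °C".
- **That FASTT values will be deleted.** The wording on excluding abnormal variability in 2.8.10 can equally mean ruling such variability out.

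**Conclusion.** The point holds as a conditional one. As written, neither the matching rule nor the stated comparison model would remove a difference in centre mix between the groups. With equal mixes there is no expected bias. With assumed centre shares of 2–10% of variance, the 5% error rate rises to about 6–11% under a random imbalance. It reaches 16–40% only in the extreme case of a single centre supplying all controls. Both the variance shares and the mixes are assumptions, because the article gives no figure for either.

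The effect is confined to the exploratory surgery-versus-control comparison. It matters most for FASTT and skinfolds, then for caesarean section and NICU admission, and less for masked CGM. The primary association and its sample size of 95 are not affected by this point. The change is worth making because it is cheap and its matching part cannot be added after recruitment.

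**What to change.** - **Sections 2.1, 2.5.2 and 2.8.1:** add centre to the matching log. Look first for a control at the surgical woman's own centre within the existing age and BMI tolerances. Use another centre only if none is available before 12 weeks.
- **Section 2.9.2, Exploratory Comparative Analyses:** include centre, fixed or random, in the surgery-versus-control models, whether or not it tests as different between groups.

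The cost is one log field, one model term and somewhat slower matching for some women. If control recruitment is already well advanced, the model term can still be added, but it works only as far as both groups are represented within centres.

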### 2.6. Safety

All (serious) adverse events (S)AEs will be recorded on applicable standardised reporting forms and associated with the subject identification number, with more detailed description of the event. SAEs will be reported onwards to the sponsor, central Medical Ethics Review Committee, and national competent authorities as required.

CGM will be conducted in a masked setting utilising a blinded receiver. As such, no real-time access to glucose data will be available to participants or clinicians, and glucose values will not be used to guide clinical decisions within the study. Consequently, specific thresholds for hypoglycaemia that would prompt clinical intervention have not been defined in the protocol. Any necessary management of hypoglycaemia will fall under routine clinical care, independent of study procedures.

### 2.7. Discontinuation of Participation

Participants may withdraw consent at any time. If a participant cannot be reached for a scheduled visit, efforts will be made to contact her and any provided alternate contacts. Premature discontinuation will occur for participants experiencing adverse events or starting long-term corticosteroid treatment after inclusion, at the investigator’s discretion, as this may affect glycaemic values and interfere with CGM interpretation (intermittent prophylactic steroid use for foetal lung maturation is allowed). Noncompliance (e.g., missing study visits, or not returning CGM materials) may also lead to discontinuation, at the investigator’s discretion.

### 2.8. Study Visits and Data Collection

An overview of timing of enrolment, interventions, and assessments in the study is provided in Table 1.

#### 2.8.1. Screening Visit

The study will be introduced at first prenatal visit by a physician or midwife. Interested women will receive a summary information sheet and the informed consent form. Women will have at least 24 h to consider their decision, after which the local research team will follow up on their choice. Informed consent can only be signed if all inclusion and exclusion criteria have been met. Pregnant women can only participate in the control group if a one-on-one match is identified with a participant in the surgical group. The coordinating investigator will maintain a password-protected log containing BMI and age data for all study participants to ensure accurate matching.

#### 2.8.2. Visit 1 to 4

Women will be recruited at first prenatal visit (before 12 weeks). To evaluate glucose homeostasis, a masked CGM will be used for 10 days at the following time points: between 6 and 12 weeks of pregnancy, at 18–22 weeks of pregnancy, at 24–28 weeks of pregnancy (when screening for GDM, and at 30–34 weeks of pregnancy. At each visit with CGM, clinical examination will be performed, questionnaires will be completed, and micronutrients will be measured (as described below). As standard of care in the surgical group, follow-up by a dietician during pregnancy will be provided according to need or at the indication of the treating physician. A purpose designed multivitamin preparation (BariNutrics^®^ Prenatal) will be started at periconception. In each trimester, micronutrients will be checked by blood analyses of vitamin A, vitamin D, B12, folate, prothrombin time iron, transferrin saturation, and ferritin, for the surgical group. Deficiencies detected at any time point will be addressed by the prescription of targeted extra supplementation by the treating physician.

A standardised protocol will be used to screen for diabetes in early pregnancy and GDM later in pregnancy for both groups.

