#### 2.8.4. Biochemical Parameters and GDM Screening

Lab measurements will be performed in line with normal routine. Based on recommendations for micronutrient monitoring during pregnancy after MBS, vitamin A (µg/L), 25-OH-Vitamin D (µg/L), vitamin B12 (ng/L), folate (µg/L), prothrombin time (s, %, INR), iron (µg/dL), transferrin saturation (%), and ferritin (µg/L) will be measured every trimester in the surgical group [34]. Micronutrient monitoring in the control group will be conducted based on clinical judgement.

At first prenatal visit, screening for overt diabetes will be performed using fasting plasma glucose (FPG, mg/dL), or HbA1c (%) if fasting is not feasible. Women with a history of bariatric surgery will undergo screening for GDM at 24–28 weeks of pregnancy and will perform SMBG for a maximum of one week, as previously described [34]. At 24–28 weeks, the control group will be screened using a 50 g glucose challenge test. However, women with a history of GDM, obesity, or impaired fasting glycaemia in early pregnancy will undergo a 75 g OGTT, according to the 2019 Flemish guidelines [35]. An overview of diagnostic criteria for GDM in both groups is provided in Supplemental Table S1.

Specifically for this study and for all participants, at each study visit (6–12 weeks, 18–22 weeks, 24–28 weeks, and 30–34 weeks) and at delivery when cord blood is collected, two additional plasma samples will be collected for long-term storage at the biobank of UZ Leuven to allow for future analysis of metabolomics.

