	**Clinical and biochemical outcomes:**						
	Physical examination	X	X	X	X	X	
	BIA measurement mother		X				
	(S)AE collection		X	X	X	X	X
	foetal ultrasound		X	X		X	
	SMBG for 1 week surgical cohort				X		
	50 g GCT or 75 g OGTT control group				X		
	Skinfold measurements newborn						X
	Lab with micronutrients measurement		X	X		X	
	Lab with fasting plasma glucose or HbA1c		X				
	Metabolomics on maternal plasma		X	X	X	X	X cord blood

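### A control-only glucose load is scheduled alongside the 24–28 week CGM session with no rule on its handling, so it can modestly inflate control variability and time above range in the exploratory comparison

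*Protocol article*

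**What the plan says.** - **CGM session.** Section 2.8.2 states that "a masked CGM will be used for 10 days at the following time points", and gives the third of the four time points as "at 24–28 weeks of pregnancy (when screening for GDM".
- **Screening test in controls.** Section 2.8.4: "At 24–28 weeks, the control group will be screened using a 50 g glucose challenge test". The exception is that "women with a history of GDM, obesity, or impaired fasting glycaemia in early pregnancy will undergo a 75 g OGTT".
- **Screening in surgical women.** The same section says that they "will perform SMBG for a maximum of one week". No glucose load is given.
- **Schedule.** Table 1 has a row "50 g GCT or 75 g OGTT control group" marked in the 24–28 week column, where masked CGM is also marked.
- **Use of the data.** Section 2.3.3 lists SD, CV, MAGE and time above 120, 140 and 180 mg/dL among the outcomes for both groups. Section 2.9.2, under exploratory comparative analyses: "The comparison between the MBS and control group on birth weight and glycaemic measures will be performed using linear mixed models".
- **Purpose of masking.** Section 2.8.9 explains that the sensor is blinded so that women keep to their usual behaviour and the traces are unbiased.

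The article gives no order for test and sensor in controls and no rule for readings taken around the test.

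**The concern.** One arm of the comparison may have a test-induced glucose excursion in its trace and the other cannot. Controls are matched to surgical women on pre-pregnancy BMI, so those matched to women who still have obesity will have obesity themselves and take the larger load. The metrics being compared are the ones that a load moves: SD, CV, MAGE and time above a threshold.

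If the load is recorded, the error affects controls only and pushes these metrics upward. It would therefore hide part of any excess of variability or hyperglycaemia after surgery. The first exploratory objective, comparing glucose metabolism between the groups, is the one at stake. A 50–75 g load is also not the everyday behaviour that masking is meant to preserve.

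**Working it through.** **Is any stated figure involved?** No. The planned n = 95 was reproduced only to see whether controls enter it. Fisher z for r = 0.3, two-sided alpha 0.025, 80% power: ((2.241 + 0.842)/atanh(0.3))² + 3 = 102.2. Adding 4 covariates gives 106.2. Multiplying by 2.5/4 (design effect 1 + 3 × 0.5 = 2.5, four measurements) and dividing by 0.7 gives 94.8, so 95. Controls play no part in it.

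**Inputs**
- From the article: session length 10 days = 240 h; four sessions = 960 h.
- Assumed, not in the article: post-load excursion of 2–3 h, averaging d = 40–50 mg/dL above usual; usual session mean 100 mg/dL and SD 18 mg/dL.

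**Share of the session.** p = 2/240 = 0.83%, or 3/240 = 1.25%.

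**Session mean.** Shift = p × d, from 0.0083 × 40 = 0.33 to 0.0125 × 50 = 0.63 mg/dL.

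**Session SD.** New SD = √(18² + p(1 − p)d²):

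| Excursion | d (mg/dL) | New SD | Rise |
|---|---|---|---|
| 2 h | 40 | 18.36 | 2.0% |
| 2 h | 50 | 18.57 | 3.1% |
| 3 h | 40 | 18.54 | 3.0% |
| 3 h | 50 | 18.84 | 4.7% |

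**CV.** From 18.0% to between 18.36/100.33 = 18.3% and 18.84/100.63 = 18.7%.

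**Time above a threshold.** The ceiling is p itself, 0.83–1.25 points. It is reached only if every minute of the window exceeds the threshold and none would have done so otherwise. For a less extreme figure, take the window as normal with mean 140–150 mg/dL and SD 20 (assumption):
- Above 140: 50–69% of the window, so 0.42–0.86 points.
- Above 180: 2.3–6.7% of the window, so 0.02–0.08 points.

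**Wider assumptions.** With a window of 1–3 h, an excursion of 20–60 mg/dL, session mean 95–105, session SD 15–22 and within-window SD 20, the mean shifts by 0.08–0.75 mg/dL. SD rises by 0.03–1.48 mg/dL (0.1–9.9%) and CV by 0.01–1.42 points. The top of the range needs the longest window, the largest excursion and the lowest usual SD together.

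**Dilution.** All figures are for one woman whose test falls within the wear. If only a fraction f of controls are in that position, the group mean shift is f times as large; at f = 0.5 it is 0.17–0.31 mg/dL. Pooled over all four sessions, the ceiling on time above a threshold is 2/960 to 3/960, or 0.21–0.31 points, and the mean shift is a quarter of the single-session value, 0.08–0.16 mg/dL.

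MAGE was not calculated. It depends on how many qualifying excursions the session contains. A load excursion can only count among the larger ones.

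**The case against.** **The timing is not fixed.** Test and sensor share a four-week window and a column in Table 1, but nothing places the test inside the ten days of wear. It could precede insertion or follow removal. This stands: a reader might infer that control metrics are inflated, and the text supports only that they can be.

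**An article condenses.** Sensor logistics and CGM cleaning may be set out in the full protocol or site procedures, and section 2.8.2 refers to a standardised screening protocol for both groups. This is fair, and the point is not put as a missing detail. It is that the schedule places a control-only load beside a CGM session used for a group comparison, and that a simple rule would remove the effect.

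**The effect is small and gross.** The test may replace a meal that would itself have raised glucose, and any fast before an OGTT lowers it. Both reduce the net shift, and neither is in the arithmetic above. This stands.

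**Stronger readings fail.** One might infer that the artefact could reverse the group difference. The article gives no expected difference, and shifts of this size do not support that. One might also expect time above 180 mg/dL to suffer most, but under the central assumptions little of the window reaches that level.

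**The placement has a reason.** Section 2.3 includes an objective comparing CGM with SMBG for GDM screening after surgery, and section 2.8.9 cites alignment with routine care. Both justify the timing in surgical women. Neither requires the control trace to include the load.

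**Conclusion.** The point holds as a possible, one-directional and modest artefact. If the load falls within the wear, control SD, CV, MAGE and time above 120 and 140 mg/dL at 24–28 weeks can be inflated. Under the assumed excursions the mean moves by less than 1 mg/dL, SD by about 2–5%, and time above a threshold by at most 0.8–1.25 points, less in net terms. The time-above metrics are the most exposed in relative terms: if usual control time above 140 mg/dL were 3% (assumption), the ceiling would be a rise of 0.83/3 to 1.25/3, or 28–42%, at that visit.

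The consequence is some narrowing of any surgical excess in one of four sessions of a comparison labelled exploratory. A reader might carry the concern over to the main results. The documents do not support that: the primary and secondary analyses use the surgical group only, which takes no load, and n = 95 does not depend on controls. Excursion size and duration, usual mean and SD, and the fraction of controls tested during wear are all assumptions.

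**What to change.** Record the date and time of each control's GCT or OGTT relative to sensor insertion. Then, for the between-group comparison, adopt one of these rules:

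1. Start the control's 24–28 week sensor after the test is finished. This loses no data but works only for sessions still to come.
2. Exclude the test-period readings before metrics are computed: either any pre-test fast plus the post-load hours, or the whole test day. This also works for sessions already recorded, provided the test time is known.
3. At the least, report the comparison with and without those readings.

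The cost is one line in the visit procedure or one filter in the CGM export. Dropping the whole day loses up to one day of ten in controls at one visit, to remove an excursion of about 1% of the session. Excluding only the fast and the post-load hours loses less. The screening tests themselves and the surgical-group analyses are unchanged.
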